## Intervention

All patients will be treated using IMRT (with pre-specified image guidance protocol as per institutional standards).

## Arm 1

Patients will receive standard care and serve as external controls, representing typical clinical practice. Their cases will be reviewed in the head and neck multidisciplinary clinic, following the institutional approach. These patients will undergo treatment analogous to that of ‘Arm 2,’ but with allowances for protocol deviations at the discretion of the treating radiation oncologist.

## Arm 2

The prescribed radiotherapy dose will be 70 Gy, delivered in daily fractions of 2 Gy. The elective volume will receive 50 Gy, administered in 2 Gy daily fractions over the first 5 weeks. This will be followed by a boost to the high-risk volume, delivering an additional 20 Gy in 2 Gy daily fractions over the subsequent 2 weeks. The entire treatment will be delivered in a phased approach using sequential planning.

## Arm 3

The radiation dose will be similar to ‘Arm 2’. In addition, the HSV identified on baseline FMISO scans will be contoured and an isotropic margin of 3 mm will be given. This volume will be boosted in phase II to a total dose of 80 Gy. (Addition of 30 Gy in 3 Gy daily fraction added in phase II as a simultaneous integrated boost – SIB) (Figure 2). The BED and EQD2 for Arm 3 (to HSV) are 99 Gy_10_ and 82.5Gy, respectively, in comparison to 84 Gy_10_ and 70 Gy, respectively, in Arm 2.

## Contouring protocol

The patients will be immobilised using a four-clip thermoplastic cast (Orfit Ray™ Cast) as per standard institutional protocol. The treatment planning scans will be performed with IV contrast and 3 mm slice thickness. Daily IGRT is not mandatory but recommended. The daily shift should be at most 5mm of the planning target volume in any axes.

Arm 2 and 3: Gross tumour volume (GTV) will be delineated using MRI and FDG PET CT per standard institutional standards. Clinical target volume (CTV 1) will include GTV based on clinical and radiologic information (including primary tumour and involved lymph nodes), expanded with isotropic 5-mm margins. Clinical target volume (CTV 2) will consist of the high-risk areas harbouring microscopic disease and elective nodal regions. CTV 2 will be created individually for the primary target and the secondary lymphatic. A 5 mm margin will be added to each CTV 1 and 2 to form planning target volume (PTV) 1 and 2, respectively. A model dose of 50 Gy in 25 fractions will be prescribed to PTV 2 in phase I and 20 Gy in 10 fractions to PTV 1 in phase II.

Hypoxic sub-volume delineation (Arm 3): The HSV delineation will be done for patients in arm 3 using baseline FMISO. The HSV will be contoured as per baseline FMISO and adjusted according to the second FMISO scan done between the fourth and the fifth week of radiation treatment. A planning CT will also be repeated at the time for adjusting the HSV to account for temporal changes. The HSV, thus, delineated will be isotropically enlarged by 3 mm to form a biological target volume (BTV). The BTV will be truncated from bone, air and organs at risk (OAR) by 3mm. The BTV will be prescribed 30 Gy in 10 fractions.

Adjusting HSV in phase 2*:* The HSV will not be adapted based on the response, but will be adjusted only to account for geometrical changes due to image registration in the new scan taking into account – OARs, air and bone. The boost volume will primarily remain consistent with the baseline HSV.

Organ at risk: Dose constraints to OAR and planning risk volume will be taken from quantitative analysis of normal tissue effects in the clinic (QUANTEC) and RTOG protocols (wherever QUANTEC did not provide constraints). The patients in ‘Arm 3’ will be subjected to isotoxic dose escalation, with constraints remaining the same as Arm 2.

Treatment planning: All patients will be treated on TrueBeam™ version 1.6 (Varian Medical Systems Inc., Palo Alto, CA, USA) equipped with HD-120 leaf MLC (28 pairs of 5 mm and 32 pairs of 2.5 mm). Plans were made on Varian Eclipse™ Version 15 (Varian Medical Systems Inc., Palo Alto, CA, USA) using 7–9 co-planar static fields with collimator angle 0. IMRT plans will be optimised using a dose-volume optimiser and calculated using the Anisotropic Analytical Algorithm.

## Adherence to protocol and concomitant care

Patients will be monitored weekly to assess their tolerance to treatment. Any patient exhibiting grade 3 or higher toxicity will require urgent therapeutic intervention. The most anticipated side effects are mucositis and dysphagia. Patients will be evaluated weekly for the need for nutritional support and feeding tube placement, as well as on an as-needed basis. In rare instances of severe toxicities not responding to conservative measures, a treatment break may be necessary. The resumption of radiotherapy will be contingent upon the resolution of major toxicities, with the aim of restarting radiotherapy as soon as clinically feasible.

Outcome measures: Oncological outcomes will be collected by a designated team of head and neck specialists (radiation oncologist, surgeon and radiologist)

Response assessment*:* The patients would be assessed for the first time after 12 weeks of completion of definitive radiotherapy. The patients would be assessed by 18-FDG PET CT (± MRI) and direct laryngoscopy. The need for biopsy versus repeat imaging at a short interval will be taken by a multispeciality clinic taken into view the clinical examination, laryngoscopy findings (including narrow band imaging) and radiological findings.

*Primary endpoint: locoregional control* (LRC): LRC is defined as the absence of tumour recurrence or progression within the primary tumour site and the regional lymph nodes, as determined by clinical evaluation, imaging studies and/or biopsy confirmation. LRC will be assessed at predefined time points, with the primary time point being 2 years post-treatment. Locoregional recurrence within 2 years post-treatment is associated with significant morbidity and reduced quality of life. Therefore, 2-year LRC serves as a clinically meaningful endpoint to guide treatment decisions and optimise outcomes for patients receiving escalated radiation doses.

### Secondary endpoints

*Overall Survival (OS)*: The duration of OS is defined as the time from the date of randomisation to death from any cause. If there is no death, the OS duration will be censored at the time of analysis.

*Locoregional relapse-free survival (LRFS)*: LRFS is defined as the time from the date of randomisation to the first histopathologically confirmed relapse of locoregional disease. If there is no confirmed recurrence, the LRC duration will be censored at the time of analysis. Death from any cause will be considered as an event in LRFS.

*Acute toxicity:* Acute adverse events will be assessed and recorded according to the NCI CTCAE version 5.0 [40]. Evaluations will be conducted at baseline, mid-treatment (week 4), immediately post-treatment, 2 weeks post-radiotherapy and subsequently at 3 months post-treatment.

*Late toxicity assessment*: Long-term toxicities of the upper aerodigestive tract will be recorded at 1 and 2-year follow-ups. They will be assessed using the RTOG long-term toxicity assessment [41].

*Patient-reported outcome*: The data will be collected by the trial coordinator and, research nurse by collecting proformas filled by patients.

European Organisation for Research and Treatment of Cancer (EORTC) head and neck questionnaires: The Hindi versions of the EORTC QLQ-C30 [42] and QLQ-H and N35 questionnaires [43, 44] will be obtained from the QoL unit, EORTC Data Centre in Brussels, Belgium. The EORTC QLQ-C30 questionnaire consists of five functional scales that include physical, role, cognitive, emotional and social; three symptom scales that include fatigue, pain and nausea/vomiting; a global QoL scale; and six single items that include dyspnea, insomnia, appetite loss, constipation, diarrhoea and financial difficulties. The QLQ-H and N 35 questionnaires consisted of seven multiple-item scales that assess the symptoms of pain, swallowing ability, senses (taste/smell), speech, social eating, social contact and sexuality and six single-item scales that assess the presence of symptomatic problems associated with teeth, mouth opening, dry mouth (xerostomia), sticky saliva, coughing and feeling ill. All the scales of the EORTC QLQ-C30, QLQ-H and N35 range from 0 to 100.

Dysphagia assessment: Dysphagia is commonly evaluated through functional assessments of swallowing, such as videofluoroscopy or fiberoptic endoscopic evaluation. Furthermore, tools that quantify the severity and impact of dysphagia are essential for determining treatment outcomes and rehabilitation requirements. Various instruments are available for assessing dysphagia, including the 10-item Eating Assessment Tool [45], the Sydney Swallow Questionnaire [46], the Swallowing Quality of Life Questionnaire (SWAL-QOL) [47] and the MD Anderson Dysphagia Inventory (MDADI) [48]. The MDADI includes global, emotional, functional and physical subscales, each designed to capture different aspects of how dysphagia impacts quality of life. The global assessment question provides a straightforward method for evaluating overall dysphagia severity. It was specifically chosen because of its relatively shorter 20-point questionnaire and easier implementation, especially when compared to SWAL-QOL or dysphagia handicap index [49].

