## Sample size

Estimated LC rates 59% and 84% in the control and treatment arm, respectively, in the phase II study by Welz *et al* [29]. For achieving an 80% power (i.e., 1−β = 0.8) at the 5% level of significance (i.e., α = 0.05) with the equal allocation (i.e., k = 1), the sample size for Arm 2 and 3 is 62 patients in each arm. This study is designed as a Phase II trial aimed at evaluating the preliminary efficacy and safety of the intervention. As such, the primary focus is on detecting a signal of LRC rather than establishing a long-term survival benefit. The sample size of 124 participants (62 per group) is consistent with Phase II study designs, which typically involve smaller cohorts to efficiently assess early efficacy. Due to the exploratory nature of this trial, the follow-up period was set at 2 years to capture early control rates, which are increasingly recognised as predictive of long-term outcomes in salivary ductal cancers. The 2-year endpoint aligns with the study’s goal of generating data to inform the feasibility of subsequent Phase III trials.

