### Data collection and analysis

All data will be collected in the central registry of the institute and anonymised. All statistical analyses were performed using the Statistical Package for Social Science System (SPSS v26, SPSS Inc, Chicago, IL) or equivalent software. Continuous variables will be written as mean (along with standard deviation) and median (along with interquartile range). Categorical variables will be represented as frequencies and percentages. Inter-cohort testing will be performed using chi-square for categorical variables and independent-t/nonparametric tests for continuous variables. Time-to-event endpoints will be measured from the date of randomisation to the date of failure or last follow-up. The LRC rate at 2 years will be estimated using the Kaplan–Meier method, with the time to locoregional failure defined as the duration from the start of radiation therapy to the first documented recurrence or progression within the primary tumour site or regional lymph nodes. The LRFS and OS, as mentioned earlier, death from any cause will be considered a failure. The LRFS and the OS rates will be estimated using the Kaplan–Meier product-limit method for each arm. Their distributions will be compared between treatment arms (Arms 2 and 3) with a two-sided log-rank test ≤ 0.05. The clinicopathological characteristics, survival outcomes and treatment modalities will be analysed using the univariate and multivariate Cox proportional hazards model. All eligible patients will be included in the analysis in the arm to which they were randomly assigned (intent-to-treat).

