### Oversight and data monitoring committee

Organisational structure, protocol revision, publication and managing general administrative function will be carried out by principal investigator and co-principal investigator. A separate trial committee (see title page for members) will be tasked to ensure quality checks on the radiation plan, data entry and 6-monthly report and audit. Any unexpected or grade 5 toxicity will be reported to the Serious Adverse Events (SAEs) Committee, which will monitor and evaluate the potential causes of these adverse effects.

Recruitment strategy: The trial will be conducted at a tertiary care centre specialising exclusively in oncology. Based on the annual case volume managed by the head and neck multispecialty clinic, the projected sample collection is expected to be completed within 2 years.

Retention strategy: Patients will be advised on the importance of maintaining diligent follow-up and completing the health-related quality of life questionnaire. In the event of a missed follow-up, efforts will be made to contact patients via telephone, including offering video consultations, to ensure the completion of the required forms. Long-term care will be provided to those whose side effects are considered to be beyond standard of care treatment, as assessed by the SAE committee.

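### The endpoint definitions and the analysis section give different censoring dates for OS and LRFS when a patient is lost before the analysis

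*Protocol article*

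**What the plan says.** The protocol article states a censoring rule in two places.

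- **Secondary endpoints, OS:** "If there is no death, the OS duration will be censored at the time of analysis".
- **Secondary endpoints, LRFS:** "If there is no confirmed recurrence, the LRC duration will be censored at the time of analysis". The sentence sits inside the LRFS definition but names LRC, which is the abbreviation of the primary endpoint. The next sentence makes death from any cause an LRFS event.
- **Data collection and analysis:** "Time-to-event endpoints will be measured from the date of randomisation to the date of failure or last follow-up". This sentence is general and excludes no endpoint.

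The same analysis section then names the methods that use these times: "The LRFS and the OS rates will be estimated using the Kaplan–Meier product-limit method for each arm", and "Their distributions will be compared between treatment arms (Arms 2 and 3) with a two-sided log-rank test ≤ 0.05".

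On follow-up, the Sample size section says that "the follow-up period was set at 2 years to capture early control rates". The retention strategy, under Oversight and data monitoring committee, says: "In the event of a missed follow-up, efforts will be made to contact patients via telephone, including offering video consultations". No expected loss to follow-up is stated, and no OS or LRFS rate is assumed for planning.

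**The concern.** Kaplan–Meier and the log-rank test assume that a patient counted as at risk at a given time is under observation then, so that an event would be seen. Censoring an event-free patient at the analysis date breaks this for anyone lost earlier. The patient stays in the denominator, while a death or relapse after the loss goes unrecorded. The resulting bias in the survival estimate is upward.

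Two things are at stake. First, the same data can give two sets of OS and LRFS results, depending on which section the analyst follows, and the choice could be made after the data are seen. Second, if the endpoint definitions are followed literally, survival is overstated in each arm by an amount that depends on that arm's loss. The arm that loses more patients looks better. The trial is open-label with different treatment in Arms 2 and 3, so unequal loss is possible, although nothing in the article says that it is expected.

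**Working it through.** **1. The two rules side by side.** The plan states no figure on this point, so there is none to reproduce. Take a hypothetical patient last seen event-free 8 months after randomisation, in an analysis run when that patient would be at month 30.

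- Under Secondary endpoints, the patient is censored at month 30.
- Under Data collection and analysis, the patient is censored at month 8.

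The rules agree only for patients followed up to the analysis. For everyone else they differ by the whole unobserved period (22 months here).

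**2. Size of the bias if the endpoint definition is applied literally.** All inputs are assumptions, because the article gives neither a loss rate nor an OS or LRFS rate:

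- constant event hazard λ, with true 2-year survival S, so λ = −ln(S)/2 per year;
- constant loss hazard μ, independent of prognosis, with cumulative loss L over 2 years, so μ = −ln(1 − L)/2;
- events after loss are never learned of;
- all patients reach 2 years before the analysis, so lost patients remain in the risk set throughout.

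The apparent 2-year survival is then one minus the probability that an event occurs before loss:

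apparent S = 1 − [λ/(λ + μ)] × [1 − exp(−2(λ + μ))]

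Since exp(−2(λ + μ)) = S × (1 − L), the last bracket is 1 − S(1 − L).

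For S = 0.60, 2λ = 0.5108.

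- L = 5%: 2μ = 0.0513; λ/(λ + μ) = 0.5108/0.5621 = 0.9088; last bracket = 1 − 0.57 = 0.43. Apparent S = 1 − 0.9088 × 0.43 = 0.609.
- L = 20%: 2μ = 0.2231; λ/(λ + μ) = 0.5108/0.7340 = 0.6960; last bracket = 1 − 0.48 = 0.52. Apparent S = 1 − 0.6960 × 0.52 = 0.638.

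Bias in percentage points over a range of assumptions:

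| True 2-year survival | 5% loss | 10% loss | 15% loss | 20% loss |
|---|---|---|---|---|
| 50% | +1.1 | +2.3 | +3.4 | +4.6 |
| 60% | +0.9 | +1.9 | +2.8 | +3.8 |
| 70% | +0.7 | +1.4 | +2.2 | +2.9 |

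**3. Unequal loss with no true difference.** With S = 60% in both arms and loss of 5% in one and 20% in the other, the apparent rates are 60.9% and 63.8%, a false difference of 2.9 points. With 5% v 15%, or 10% v 20%, it is 1.9 points.

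**4. Under the analysis section's rule.** If patients are censored at last follow-up and loss is unrelated to prognosis, Kaplan–Meier estimates the true survival and this bias is zero.

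**5. Scale.** With 62 patients per arm and survival near 60%, the standard error of a difference between two proportions is about √(2 × 0.60 × 0.40/62) = 0.088, or 8.8 points. A false difference of 2.9 points is about one third of that (2.9/8.8 = 0.33).

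**The case against.** The strongest reply is that the plan already contains the conventional rule. The analysis section ends observation at last follow-up for all time-to-event endpoints, and that section also names the estimator and the test. Censoring at the time of analysis may be no more than shorthand for administrative censoring at data cut-off. The endpoint definitions do not mention lost patients, let alone say that they are taken to be event-free. In addition, telephone and video contact are planned after missed visits, so some later events would be learned of and the bias would be smaller than the model shows.

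Much of this stands. A reader might infer that the trial will overstate survival. The article does not support that as a flat statement: the overstatement follows only if the endpoint definitions are applied literally, against the analysis section.

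A reader might also infer that the primary endpoint is affected, because the LRFS sentence speaks of LRC and because the abstract defines LRC in nearly the words used later for LRFS. That too goes further than the text. The sentence stands between two others about LRFS. The primary endpoint is defined separately, and its Kaplan–Meier analysis is described in the analysis section without any such rule. The abstract contains no censoring rule. A leftover or mistaken label is the likelier explanation.

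What does not stand is the idea that nothing needs changing. The shorthand reading is not written down. The sentences in Secondary endpoints are the only ones that use the term censored, and they make no exception for patients lost early. This is a contradiction between two stated rules, not a detail left to an unseen analysis plan.

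**Conclusion.** The inconsistency is real and should be fixed. It mainly concerns two secondary endpoints, and it is not grave enough to put the trial's main conclusion in doubt.

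The contradiction itself rests on the text alone. The size of its consequence rests on assumptions: exponential event and loss times, loss independent of prognosis, no events learned of after loss, and complete 2-year potential follow-up. Under these, literal use of the endpoint definitions overstates 2-year OS or LRFS by 0.7 to 4.6 points for true survival of 50% to 70% and loss of 5% to 20%. Unequal loss of 5% v 20% at 60% survival adds a false difference of about 2.9 points. That is modest beside the sampling error with 62 per arm. Under the last-follow-up rule, none of it arises.

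**What to change.** In Secondary endpoints, bring the two censoring sentences into line with Data collection and analysis:

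- **OS:** censor patients not known to have died at the date last known alive, and no later than the data cut-off.
- **LRFS:** censor patients without an event at the last follow-up at which they were known to be alive and free of locoregional relapse, and no later than the data cut-off.
- **Label:** replace *LRC duration* in the LRFS sentence with *LRFS duration*, so that it cannot be read as setting the censoring rule for the primary endpoint.

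The two dates can differ for the same patient. A telephone contact may establish that a patient is alive without establishing freedom from relapse. Censoring LRFS at the last formal disease assessment is another convention, but it may not match the last-follow-up date in the analysis section, so the wording above is preferable here.

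The cost is two sentences and one label. The analysis section already requires a last-follow-up date. The article reports that recruitment was still under way, so the change could precede the analysis. The only downside is that reported survival may be slightly lower than under the literal wording of the endpoint definitions.

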**Methods:**

The dose-escalated hypoxia-adjusted radiotherapy trial is an open-label, parallel, randomised, single-centre, phase II study. Patients with HNC will undergo [18F]. FMISO PET CT to identify hypoxic regions. Normoxic patients will be labeled as Arm 1 and will not be part of the primary assessment. Patients with hypoxia will be stratified into two arms (2 and 3). Arm 2 will receive standard radiotherapy of 70 Gy in 2 Gy fractions, while Arm 3 will receive an additional boost to the hypoxic sub-volumes, delivering a total of 80 Gy (Phase 2). All patients in Arms 2 and 3 will also receive concurrent chemotherapy with cisplatin. Patients will be monitored weekly for treatment tolerance, with acute adverse events recorded according to National Cancer Institute Common Terminology Criteria for Adverse Events v5.0. The primary endpoint is LRC, defined as the time from randomisation to the first histopathologically confirmed relapse of locoregional disease. Secondary endpoints include OS, locoregional relapse-free survival, acute and late toxicity and patient-reported outcomes assessed using the European Organisation for Research and Treatment of Cancer QLQ-C30 and QLQ-H&N35 questionnaires.

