## Study/Trial design

DE-HyART is an open-label, parallel, randomised, single-centre, phase II study designed to evaluate the effectiveness and feasibility of dose escalation using FMISO PET scans for HNC. This superiority trial aims to assess the impact of integrating IMRT with simultaneous integrated boost (SIB) and dose escalation to hypoxic sub-volumes, as delineated by [18-F] FMISO, compared to standard-dose radiotherapy. The treatment protocol also incorporates concurrent chemotherapy with standard dosing of the physician’s choice and patients’ fitness. The protocol has been developed in accordance with SPIRIT guidelines [34, 35].

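### LRFS counts a locoregional relapse only if histology confirms it, while the detailed LRC text does not require histology, so a patient can fail LRC and still be event-free for LRFS

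*Protocol article*

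**What the plan says.** Four places in the protocol article bear on what counts as locoregional failure.

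- **Secondary endpoints, LRFS.** "LRFS is defined as the time from the date of randomisation to the first histopathologically confirmed relapse of locoregional disease". It adds that "Death from any cause will be considered as an event in LRFS" and that "If there is no confirmed recurrence, the LRC duration will be censored at the time of analysis". The last sentence names LRC although it stands in the LRFS definition.
- **Adherence to protocol and concomitant care, primary endpoint.** LRC is the absence of locoregional recurrence or progression, "as determined by clinical evaluation, imaging studies and/or biopsy confirmation". Biopsy is one of several sufficient grounds.
- **Data collection and analysis.** Time to locoregional failure runs to "the first documented recurrence or progression within the primary tumour site or regional lymph nodes". Biopsy is not mentioned, and the clock starts at radiotherapy. The same section specifies a two-sided log-rank comparison of Arms 2 and 3 for LRFS and OS.
- **Abstract, Methods.** "The primary endpoint is LRC, defined as the time from randomisation to the first histopathologically confirmed relapse of locoregional disease". This is nearly the LRFS wording, without death.

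On biopsy itself, the Response assessment paragraph says "The need for biopsy versus repeat imaging at a short interval will be taken by a multispeciality clinic".

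**The concern.** LRFS is ordinarily locoregional failure or death, whichever comes first, so every LRC failure should also be an LRFS event. The detailed definitions break that nesting: LRC failure may rest on imaging or clinical findings, but an LRFS relapse may not.

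Two things are at stake. First, LRFS is one of the two endpoints for which the article spells out a log-rank comparison. An unconfirmed failure can only remove or delay an LRFS event, so each arm's LRFS curve can only move up. Second, the trial is unblinded ("DE-HyART is an open-label, parallel, randomised, single-centre, phase II study"). An event that exists only if someone takes a biopsy depends on a decision made with knowledge of the arm.

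**Working it through.** **1. The definitions applied to three patients.** LRC follows the detailed endpoint and analysis text; LRFS follows the Secondary endpoints section.

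| Patient | LRC | LRFS as written |
|---|---|---|
| Imaging progression at month 9, no biopsy, alive at month 24 | failure, month 9 | event-free at month 24 |
| Same, but dies at month 18 | failure, month 9 | event, month 18 |
| Biopsy-proven relapse at month 9 | failure, month 9 | event, month 9 |

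The first two rows are incoherent, and showing this needs no assumption. If the abstract's LRC wording is used instead, the first patient is event-free on both endpoints and the mismatch disappears.

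**2. Possible size at 2 years.** The article states no LRFS rate and no share of failures without biopsy, so it has no figure of its own to reproduce. The inputs are:

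- From the Sample size section: 59% (Arm 2) and 84% (Arm 3). They are labelled LC there and are used here as 2-year locoregional control.
- Assumed: exponential times; unbiopsied share u = 10–40%; median survival after failure m = 8–18 months; other-cause death 5–10% a year, acting before and after failure.

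With λ the failure hazard, μ the other-cause death hazard and ν = ln 2/m + μ the death hazard after failure (all per month):

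- LRFS with all failures counted = exp(−24(λ+μ)).
- Share failed but alive at 24 months: A = λ[exp(−24ν) − exp(−24(λ+μ))]/(λ + μ − ν).
- Overstatement = u × A.

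Central case: u = 20%, m = 12, other-cause death 5% a year.

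- μ = −ln(0.95)/12 = 0.00427; ν = 0.05776 + 0.00427 = 0.06204; exp(−24ν) = 0.25 × 0.9025 = 0.2256.
- Arm 2: λ = −ln(0.59)/24 = 0.02198. LRFS = 0.59 × 0.9025 = 53.2%. A = 0.02198 × (0.2256 − 0.5325)/(0.02626 − 0.06204) = 18.9%. Overstatement = 0.2 × 18.9 = 3.8 points, giving 57.0%.
- Arm 3: λ = −ln(0.84)/24 = 0.00726. LRFS = 0.84 × 0.9025 = 75.8%. A = 0.00726 × (0.2256 − 0.7581)/(0.01154 − 0.06204) = 7.7%. Overstatement = 0.2 × 7.7 = 1.5 points, giving 77.3%.
- Arm difference: 22.6 points before, 20.3 after. With u = 40% it is 18.1.

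Range over the assumptions:

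| | Arm 2 | Arm 3 |
|---|---|---|
| Smallest (u = 10%, m = 8, 10% a year) | 1.3 points | 0.5 points |
| Largest (u = 40%, m = 18, 5% a year) | 9.3 points | 3.7 points |
| u = 0 | 0 | 0 |

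**3. Direction of the effect on the arm difference.** With the same u in both arms, Arm 2's overstatement is 18.9/7.7 ≈ 2.5 times Arm 3's, so the difference narrows. The order reverses once u in Arm 3 exceeds about 2.5 times u in Arm 2. With u = 10% in Arm 2 and 30% in Arm 3, the overstatements are 1.9 and 2.3 points, and the difference widens from 22.6 to about 23.0.

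**4. Beyond the 2-year rate.** A death before month 24 restores the event in the 2-year rate but at a later date. The log-rank test, which uses the order of event times, is still affected.

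**The case against.** The strongest reply is that the root problem lies in LRC. The abstract defines LRC by histological confirmation in almost the words used for LRFS, and the stray mention of LRC in the LRFS censoring sentence suggests that paragraph was built on the same wording. If LRC were settled on the abstract's rule, the two endpoints would agree. This stands: a reader might infer that the LRFS mismatch survives any harmonisation of LRC, and it does not. It survives only if the detailed endpoint and analysis text is kept. Those are the operative sections, however, and keeping them leaves the LRFS definition wrong unless it too is edited.

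Three further points have force.

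- The biopsy sentence sits under the first response assessment, and its alternative is further imaging. It does not say that failure is declared without biopsy. That permission comes from the LRC definition.
- Requiring histology is a defensible choice in favour of specificity. Some imaging-only calls will be false positives, and for those exclusion is correct, so the figures above treat every unbiopsied call as a true failure.
- The effect is modest for a secondary endpoint in a trial that calls itself exploratory. The central shift of about 2.2 points compares with a standard error of about 8.4 points for the difference: √[(0.532 × 0.468 + 0.758 × 0.242)/62], without censoring.

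None of this removes the inconsistency. Either rule could be chosen, but the article applies both.

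**Conclusion.** The inconsistency is established from the text alone. Locoregional failure has one criterion in the LRFS definition and the abstract, and another in the detailed LRC definition and the analysis section. Under the detailed text, a living patient with unbiopsied progression is an LRC failure and LRFS event-free. Because the conflict lies between stated definitions, a separate analysis plan or condensation for a journal does not explain it.

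The consequence is conditional: 2-year LRFS *can* be overstated. The amounts in the working rest on assumed biopsy shares and survival times and on the planning rates holding, and they fall to zero if all failures are biopsied.

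A reader might infer that LRFS *is* overstated, and more so in Arm 2. The document does not support that. It gives no biopsy share by arm, and unblinded, discretionary biopsy is a reason the shares could differ. Narrowing of the arm difference is the expected direction only if biopsy practice is similar in both arms.

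**What to change.** 1. Reconcile the abstract, the primary endpoint paragraph, the LRFS definition and the analysis section to one locoregional failure rule. State one dating rule for it, including the time origin and the date used when failure rests on imaging or clinical findings.
2. Define LRFS as the first of that same locoregional failure or death from any cause.
3. In the LRFS censoring sentence, replace LRC duration with LRFS duration and match it to the chosen rule.
4. If the broader rule of the detailed text is kept, report histologically confirmed relapse as a sensitivity analysis.

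The cost is a few sentences and one extra analysis. No new data, visits or procedures are needed, and biopsy practice need not change. The downside of the broader rule is that some imaging-only calls may be false positives, which the sensitivity analysis would show.
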